The objectives of this trial are (1) to evaluate the impact of the ProACT platform on people with multimorbidity’s QoL and HCU (ie, the trial primary outcomes); participants in each trial arm will be compared on these variables; (2) to evaluate the cost-effectiveness of the personalized ProACT CareApp with care network and triage support in comparison to the nonpersonalized ProACT CareApp and control group; (3) to explore via a mixed methods approach (analysis of system and questionnaire data and interviews with participants) the potential impact of ProACT on multimorbidity self-management; (4) to evaluate the impact of the ProACT platform on informal caregivers’ caring burden; and (5) to evaluate participants’ (people with multimorbidity and care networks) overall experiences with the ProACT platform in the management of multimorbidity. Data collected from participants in trial arms 1 and 2 will also be compared. Furthermore, to explore the impact of contextual factors (eg, participants’ conditions, age, and socioeconomic status and care network participants’ motivation to take part in the trial) on fidelity of use and use outcomes (eg, reach, uptake, and acceptability); (6) to understand how ProACT is implemented and delivered in health care settings and to identify systematic differences and variation in delivery; (7) to evaluate via the process evaluation organizational readiness to transfer and optimize a digital health solution as part of the care delivery; and (8) to evaluate whether trial outcomes can inform future analysis of the impact of digital solution implementation in practice. This protocol adheres to the SPIRIT (Standard Protocol Items: Recommendations for Interventional Trials) guidelines for clinical trial reporting (Multimedia Appendix 1) [29].

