### Data Analysis Plan

For the p-RCT primary outcomes, three types of analysis will be conducted: (1) What is the influence of ProACT on perceived QoL? (2) What is the influence of ProACT on HCU? (3) What trial arm is the most cost-effective?

To determine if significant differences exist in (1) perceived QoL between the arms and (2) HCU between the arms, a linear mixed model will be used. In this model, a 2-level structure will be applied; repeated measures of QoL or HCU will comprise the first level, and participants will comprise the second level in the hierarchy. The outcomes will be assessed longitudinally using fixed effects of time, treatment arm and time interaction, and other baseline covariates such as age and gender.

ProACT’s cost-effectiveness will be determined with the use of 2 economic evaluation techniques, cost-effectiveness standard and cost-utility analysis, applying the societal perspective. Societal perspective means, in general terms, the effectiveness evaluation will consider all the relevant contributors related to the participant. The 2 methods will allow the determination of the monetary value and the benefits of the intervention in health terms. For the monetary value, the HCU data will form the basis of the analysis.

Due to the questionnaire construction variation (countable and binary questions) and the time points of data collection during the trial, the analysis will make use of 3 statistical models: Poisson (countable data), logistic (binary response data), and linear regression (continuous data). The analysis will allow the observation of how ProACT affects the HCU, per arm at each trial site, and what the costs involved in this effect are for the monetary value definition. To define a 95% CI for this cost-effectiveness estimate per arm and per trial site, a sensitivity analysis will be performed, for instance, using a bootstrapping methodology.

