Indirect costs of the care network (informal care) will be calculated using data collected from the participants with multimorbidity and their informal caregivers. First, participants with multimorbidity will provide data on time spent on care by their informal caregivers. With the use of the opportunity costs method, this time will be converted into monetary value. Next, data collected from the informal caregivers, via the Zarit Burden Interview, will facilitate an assessment of the health gains of the time spent in care, considering the ProACT intervention. Indirect costs will be considered as an aggregated cost in this study.

The cost-utility analysis technique will underpin the quality-adjusted life years calculation. The quality-adjusted life years is a general measure used in economic evaluation that permits the valuation and comparison of the health gains of an intervention. For this calculation, the health-related QoL measurement instrument (EQ-E5-5L) will capture the self-perceived health status of the participant in a 5-digit code. Next, the code will be converted into a utility value (or utility weight), based on the country-specific value set. The result consists of the multiplication of the utility value with the period lived with the self-perceived condition.

For the secondary outcomes, such as the impact of ProACT on self-management, we may use structural equation modeling to determine the relevance and importance of different variables measured during the trial. Hitherto, there is no consensus on how to measure improved self-management. For this study, we may consider the concept of self-management as a composite measurement of different variables proven to be associated with the ability to self-manage chronic illnesses. Variables that are associated with improved self-management include, for instance, self-efficacy, health literacy, and disease knowledge, and therefore may be treated as latent variables. Using a structural equation model, such as confirmatory factor analysis, we will be able to identify the existence of a relationship between these variables and an overarching concept of self-management.

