Outcomes from this exploratory analysis will help to determine whether features in ProACT could be tested in future clinical trials. Outcomes from the process evaluation and their inclusion, where possible, in the aforementioned exploratory analysis may also help to determine the relationship between implementation and effectiveness, and for whom, in what circumstances, and how ProACT influences the primary and secondary p-RCT outcomes. Descriptive summary statistics will be collated on the primary and secondary outcome measures, as well as on the variables included in the exploratory analysis.

The process evaluation will draw upon a range of quantitative and qualitative data to explore the implementation of ProACT and the factors that impact upon it. Descriptive summary statistics will be collated and examined where applicable (eg, demographic and system use data for participants with multimorbidity and care network participants, partner organizations’ administrative and ProTransfer data, and participant recruitment and withdrawal data).

Interview and focus group data will also be attained to explore implementation and factors associated with it, including, for example, the perceived usability, accessibility, and acceptability of, and engagement, satisfaction, and overall experiences with, ProACT. The interviews and focus groups will be audio recorded, transcribed, and imported into NVivo (QSR International; in Ireland and Sweden) and MAXQDA (VERBI GmbH; in Belgium) for analysis. The researchers will also take brief notes during the interviews and focus groups to aid data interpretation and to identify potential themes. The interdisciplinary research team, with expertise spanning social, health, and sports psychology, human-computer interaction, and health care innovation, will actively engage in reflexive practice throughout the analysis. This collaborative approach will ensure participant voices are central while critically accounting for researchers’ potential biases shaped by their backgrounds.

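### The model described for the exploratory self-management outcome relates indicators to a construct and, as described, has no arm term, so it cannot by itself estimate the impact of ProACT

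*Protocol article*

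**What the plan says.** Objective 3 (Study Aim and Objectives) is to explore, by mixed methods, "the potential impact of ProACT on multimorbidity self-management". The data sources are system data, questionnaires and interviews. Self-management is also the first secondary outcome listed for participants with multimorbidity.

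The Data Analysis Plan takes it up as follows: "For the secondary outcomes, such as the impact of ProACT on self-management, we may use structural equation modeling". The purpose given is "to determine the relevance and importance of different variables measured during the trial". The text then notes that there is no agreed measure of improved self-management. It suggests a composite that draws on variables such as health literacy, disease knowledge and self-efficacy, possibly treated as latent. It concludes: "Using a structural equation model, such as confirmatory factor analysis, we will be able to identify the existence of a relationship between these variables". The other end of that relationship is a general self-management construct.

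The next paragraph labels the work exploratory and gives its use: "Outcomes from this exploratory analysis will help to determine whether features in ProACT could be tested in future clinical trials". It also promises descriptive summaries of the primary and secondary measures.

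For the primary outcomes, by contrast, the same section specifies a linear mixed model with "fixed effects of time, treatment arm and time interaction, and other baseline covariates such as age and gender".

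**The concern.** The question is one of impact: does self-management differ between participants given the full platform, the basic app and usual care? The one inferential method described answers a different question, namely whether several scales reflect a common construct. If the text is followed as it stands, the report on this outcome could contain factor loadings, fit indices and descriptive tables, but no estimated difference between randomised arms with its uncertainty.

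This matters because the Discussion (Strengths) expects participants with triage support, which only arm 1 receives, to gain confidence in self-management. It says such findings could support adding clinical oversight to digital services. That argument needs an arm comparison. The interviews cover arms 1 and 2 only, and arm 3 has no technology and hence no ProACT system data. The questionnaires are therefore the only described self-management data that could include the control arm.

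**Working it through.** The article gives no figure on this point, so there is nothing to reproduce. The check is a reading of the text, followed by a small illustration.

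**Step 1: question against method.**

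| Item | Primary outcomes (quality of life, health care use) | Self-management |
|---|---|---|
| Question | Differences between arms | Impact of ProACT |
| Model | Linear mixed model | Optional structural equation model; factor analysis as example |
| Arm term | Arm-by-time interaction stated | None stated |
| Time term | Stated | None stated |
| Stated product | Difference between arms | Relation of indicators to a construct |

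**Step 2: does other text supply the comparison?** The p-RCT Design section says that experimental and descriptive assessments will compare the three arms, without naming an outcome or model. The Study Aim and Objectives section says that arms 1 and 2 will also be compared, which leaves out arm 3 and again names no model. The Data Analysis Plan adds descriptive statistics. None of these is an inferential arm comparison of self-management.

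**Step 3: what a measurement model shows when there is an effect.** Assumptions, for illustration only: one factor, three indicators, true loading 0.7 (residual variance 1 - 0.49 = 0.51), equal arms, and a latent shift of *d* SD in arm 1 only. The number analysed per arm is 240 × (1 - 0.30) = 168, from the planned 240 per arm and the 30% attrition in the Sample Size Justification.

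Pooling the arms adds *d*² × (1/3) × (2/3) = 2*d*²/9 to the latent variance. The standardised pooled loading is then

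sqrt[ 0.49(1 + 2*d*²/9) / ( 0.49(1 + 2*d*²/9) + 0.51 ) ].

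- *d* = 0: sqrt(0.49 / 1.00) = 0.700.
- *d* = ±0.25: 2 × 0.0625 / 9 = 0.0139; sqrt(0.4968 / 1.0068) = 0.702.
- *d* = 0.5: 2 × 0.25 / 9 = 0.0556; sqrt(0.5172 / 1.0272) = 0.710.

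The loading depends on *d*² only, so benefit and harm of equal size give the same value. An arm contrast on the mean of the indicators has expectation 0.7*d*. A simulation with 2,000 replicates agrees:

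| Latent shift in arm 1 (SD) | Pooled loading | Arm 1 minus arm 3, indicator mean |
|---|---|---|
| -0.25 | 0.703 | -0.176 |
| 0 | 0.701 | 0.002 |
| 0.25 | 0.702 | 0.176 |
| 0.5 | 0.710 | 0.353 |

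The spread of the loading across replicates (SD about 0.04) is several times larger than the whole range of its means (0.710 - 0.701 = 0.009). The contrast follows the shift; the loading does not.

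**The case against.** The strongest reply is that the article commits to very little. The model is one that may be used, and factor analysis appears only as an example. The factor-analysis sentence can be read as an answer to the measurement problem raised just before it, not as the whole effect analysis. A structural model with arm as a predictor, or a multi-group model comparing latent means, belongs to the same class and would estimate impact. All of this stands. A reader might infer that structural equation modelling cannot answer the question, or that the trial is bound to a bare factor analysis; the text supports neither.

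A second reply is that this is only detail left to an analysis plan that is not shown, which may well contain an arm comparison. That carries part of the way. But the article does more than stay silent: it pairs an impact question with a model and states that model's purpose and product, and neither is an impact.

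A third reply is that the objective is exploratory and uses mixed methods, with descriptive summaries also planned and general statements that arms will be compared. This is correct and limits the weight of the point. It does not turn a loading into an effect.

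A reader might also infer that the composite will be chosen from unblinded results. The trial is unblinded and the composite is loosely worded, but the article does not say this. A confirmatory model tests a structure set in advance, so this is not a stated error.

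Finally, the simulation result follows from its set-up. It illustrates the logic and predicts nothing about this trial.

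**Conclusion.** The point holds in a limited form. For the exploratory secondary outcome of self-management, the only inferential method described is an optional measurement-type model without an arm or arm-by-time term. As described, it cannot by itself estimate the impact to which it is assigned. No figure in the article is wrong, and the primary comparisons of quality of life and health care use are unaffected.

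The size is qualitative: the described output contains no arm estimate, while a direct comparison could use about 168 participants per arm under the article's own attrition assumption. That feasibility rests on the self-management scales being completed at both time points in all three arms. The section on participants with multimorbidity indicates this, since all participants complete the baseline questionnaires and questionnaires are completed again at trial end. The list of scales is in Table S1 of Multimedia Appendix 2, which is not shown.

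**What to change.** Revise the self-management paragraph of the Data Analysis Plan to separate measurement from effect:

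- State that the factor model serves only to build or validate a self-management score.
- Estimate impact by comparing the three arms on each self-management scale, and on the score if one is used, at trial end with adjustment for the baseline value, in the mixed-model arm-by-time framework already given for the primary outcomes. Alternatively, include arm as a predictor of the latent variable.
- Label the comparison exploratory.
- Fix the list of scales and the definition of the score before the arm comparison is run. Ireland and Belgium have finished and submission is planned for 2026, so this should be settled before the analysis starts.

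The cost is a paragraph of text and a modest amount of extra analysis. No new data are needed if the scales are repeated in all arms. If Table S1 shows that some are not, the comparison should be confined to those that are, and the article should say so.

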### Ethical Considerations

The trial protocol has received ethics approval from 5 research ethics committees in Ireland, including the School of Health and Science at Dundalk Institute of Technology, Trinity College Dublin Faculty of Health Sciences (reference 220504), Health Service Executive Northeast (reference REC/22/026), Caredoc, and Blackrock Clinic. In Belgium, the protocol has been approved by the medical ethics committee of the University Hospital Brussels (approval EC-2022-246), while in Sweden, it has been approved by the Swedish Ethical Review Authority (approval 2023-07594-01). Potential participants will receive a PIL. All recruited participants will be required to give informed consent. Efforts will be undertaken to ensure that participants fully understand the study aims, procedures, and their rights, including the voluntary nature of participation and their right to withdraw at any time without consequence. Participants will not receive compensation for taking part. Participants will be informed about the collection and use of their personal data as per General Data Protection Regulation requirements. Comprehensive measures will be implemented to maintain participant privacy and data security, including data minimization, secure storage, controlled access, and deidentification of research datasets. This will include purposes for processing personal data, retention periods, and who data will be shared with. Data will only be shared with trial partners. Qualitative interview or focus group data and quantitative questionnaire data will be coded to participant IDs, with all qualitative transcripts reviewed and any identifying information removed. Electronic sensor data captured through the ProACT platform will be both coded and identifiable. The data that flow from the measuring devices to the device provider systems and admin platform will be coded. These data will be made identifiable within the admin platform to trial researchers as well as clinical triage nurses. It will also be identifiable on the CareApp interfaces of health care professionals and formal caregivers, if a participant agrees to this. For instance, a GP may have several patients using the ProACT platform, who will be listed in the GP’s ProACT CareApp. The GP will need to identify each patient by name. The health care professionals’ or formal caregivers’ access to their CareApp will be password-protected. The ProACT platform has been developed in compliance with General Data Protection Regulation requirements, and access will be managed and available to only those members of the teams who require access to conduct the trial and research. As the ProACT platform is a low-risk, noninvasive digital health intervention study, no formal ancillary or posttrial clinical care will be required. Participants will continue to receive routine care from their usual health care providers throughout and following their involvement in the study. Participants in the intervention arms will be informed that access to the ProACT platform and triage support (where applicable) will be time-limited to the duration of the study. Should any participant experience distress or identify health concerns during the trial, they will be advised to consult their GP or relevant care team, with trial staff trained to signpost participants to appropriate services when needed. Any significant amendments to the SEURO study protocol (eg, changes to study design, eligibility criteria, outcome measures, data collection procedures, or ethical considerations) will be formally documented, including a justification for the change and the potential implications for participants or study conduct. Amendments will be submitted to the relevant research ethics committees for review and approval prior to implementation, in accordance with national and institutional regulations. All approved amendments will be recorded in the trial registry (eg, ClinicalTrials.gov or EU Clinical Trials Register, if applicable) and communicated to all study sites, collaborators, and funders. Participants will be informed of any changes that may impact their involvement in the study, and reconsent will be sought where appropriate.

## Results

Enrollment in the trial began in September 2022. To date, the trial has been completed in Ireland and Belgium. CONSORT diagrams are provided in Figures 7 and 8, depicting the recruitment and flow of participants with multimorbidity through the trials in Ireland and Belgium, respectively. Recruitment in Sweden completed in October 2025, with final participants finishing the trial by March 2026. Trial outcomes will be submitted for publication in 2026.

**Figure 7 figure7:**
[figure not shown]
CONSORT diagram of Ireland participants with multimorbidity. CASP-19: Control, Autonomy, Self-realisation, Pleasure; HCU: health care use; QoL: quality of life; RIP: rest in peace.

**Figure 8 figure8:**
[figure not shown]
CONSORT diagram of Belgium participants with multimorbidity. CASP-19: Control, Autonomy, Self-realisation, Pleasure; HCU: health care use; QoL: quality of life; RIP: rest in peace.

## Discussion

### Principal Findings

This paper presents the protocol for the SEURO EIH trial, which will investigate the effectiveness and implementation of the ProACT platform. To the best of our knowledge, this is the first trial of its kind to evaluate the effectiveness and implementation of a digital health platform with older adults with multimorbidity. Recent studies have underscored the lack of comprehensive reviews on the implementation and evaluation of digital health platforms, noting that existing reviews adopt a narrow focus, often limited to single chronic disease management or specific elements of implementation [57,58]. The ProACT proof-of-concept trial [24,26,27] demonstrated that the digital health platform ProACT, designed with and for older people with multimorbidity and their care networks, facilitated perceived improvements in their health and well-being, self-management, and receipt of support. Building on the proof-of-concept trial, the SEURO EIH trial will provide a more definitive and in-depth assessment of the updated and refined ProACT platform as a digital solution to support multimorbidity management in older adults. The SEURO trial also builds on prior work by incorporating nurse triage support and assessing the impact of this support as a means of augmenting engagement and health and well-being outcomes. Finally, this trial will also facilitate the achievement of wider SEURO project objectives: namely, to evaluate the key factors necessary to prepare any European Union region to successfully implement and scale innovative, people-centric, digital integrated health and social care solutions for multiple disease management.

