### Study Aim and Objectives

The overall aim of the Scaling European Citizen Driven Transferable and Transformative Digital Health (SEURO) project is to evaluate key factors to prepare organizations, localities, and regions across the European Union to scale, sustain, and transfer people-centric digital integrated health and social care solutions for multiple disease management. To achieve this, an effectiveness-implementation hybrid (EIH) trial [28] will be carried out in Ireland, Belgium, and Sweden, with ProACT, with embedded process evaluations to understand the process for successful “real-world” implementation. Effectiveness will be assessed from the user perspective via perceived quality of life (QoL) and from the service perspective via health care use (HCU); implementation will be assessed using quantitative and qualitative data (eg, assessment of organization readiness, participants’ system use data, health care organizations’ administrative data, and interview data) collected as part of a process evaluation. Effectiveness will be assessed through a 3-arm pragmatic randomized controlled trial (p-RCT) in each trial site. Those in trial arm 1 will receive a personalized version of the ProACT platform, can invite people in their care network (eg, informal and formal caregivers and health care professionals) to participate with them, and will have access to clinical triage support. Those in trial arm 2 will receive a basic, nonpersonalized ProACT CareApp with no access to the care network or clinical triage, while those in trial arm 3 will continue to receive standard care.

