#### The ProACT CareApp

Accessed via an interactive device (eg, a tablet or smartphone), this app displays users’ health and well-being data as derived from the different measuring devices. To support people with multimorbidity self-managing their health and well-being, the CareApp provides feedback (eg, feedback on health status including exacerbations), tools (eg, medication management tools and goal-setting features), and personalized educational content (eg, written and visual content sourced from relevant, reliable, and trusted organizations localized by region) that is contextualized to the person’s current health and well-being status. It also provides participants with the option to self-report through a series of questions about their health and well-being (eg, for those parameters not easily measured by a sensing device, such as breathlessness and mood). An overview of features is provided in Table 1 and Figures 1-5. The primary differences in the CareApp for those in trial arm 2 are that exacerbations are not highlighted, and educational content is not contextualized to the current status, therefore representing a more standard application that might be downloaded from an app store. People with multimorbidity will be the main users of the ProACT CareApp. However, customized ProACT CareApp interfaces will also be available for care network members of participants in trial arm 1 to use on their own devices (eg, tablets, smartphones, or computers) to view the participant’s data.

**Table 1 table1:** Summary of features available within the ProACT CareApp for users with multimorbidity.

Component	Feature summary
Dashboard	Today at a Glance (Figure 1): A quick glance overview of the user’s current symptom (eg, weight and blood pressure) and well-being (eg, physical activity and sleep) status today, including any alerts detected, any measures missing (based on the participant’s care plan of how often they want to measure different parameters), progress toward an activity goal, and medications taken so far today.
Dashboard	Self-report: A series of symptoms (eg, breathlessness and chest tightness) and well-being (eg, mood and anxiety) questions. The self-report card (Figure 1) indicates how many outstanding questions are to be answered. Users can also see the responses to these questions charted.

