**Trial arm 1**
Tablet device and a suite of sensorsPersonalized ProACT CareAppInclusion of the care networkClinical triage service supportTechnical helpdesk support

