**Trial arm 2**
Tablet device and a suite of sensorsStandard ProACT CareApp with no personalizationTechnical helpdesk support

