**Trial arm 3**
Usual care (no technology)

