We anticipate that participants receiving triage support will demonstrate greater and more sustained engagement with the platform as well as improved symptom awareness and confidence in self-management. These findings could support the case for embedding light-touch clinical oversight in digital health services, especially for populations managing complex health needs. If successful, the approach could be scaled through integration with existing community nursing structures or primary care pathways, reducing the burden on acute services while preserving person-centered support. Additionally, insights from the Irish, Belgian, and Swedish contexts will inform strategies for adapting such services to different health system infrastructures.

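### The Discussion attributes effects to nurse triage, but arm 1 v arm 2 identifies only the combined package of personalisation, care network and triage

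*Protocol article*

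**What the plan says.** The Discussion of the protocol article makes two statements about triage itself.

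- Principal Findings says that the trial extends earlier work by "incorporating nurse triage support and assessing the impact of this support as a means of augmenting engagement and health and well-being outcomes".
- Strengths expects participants with triage support to show better engagement, symptom awareness and confidence, and then says: "These findings could support the case for embedding light-touch clinical oversight in digital health services". It goes on to consider scaling through community nursing or primary care.

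The arms are defined earlier. Study Aim and Objectives says that arm 2 "will receive a basic, nonpersonalized ProACT CareApp with no access to the care network or clinical triage". The section on the ProACT CareApp adds that in arm 2 "exacerbations are not highlighted, and educational content is not contextualized to the current status". The arm listing under p-RCT Design gives arm 1 the personalised app, the care network and clinical triage, on top of the tablet, sensors and helpdesk that arms 1 and 2 share. Arm 3 is usual care without technology. The Randomization section describes a single allocation to three equal arms.

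The Objective in the Abstract, and the cost-effectiveness objective under Study Aim and Objectives, describe arm 1 as a package.

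**The concern.** A claim to assess the impact of triage needs a comparison in which triage changes and the rest stays the same, or an explicit statement that the assessment is not randomised. The article offers neither where it makes the claim. The Limitations section covers self-report, use logs and lack of blinding, but not the bundling.

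The stake is how the result is read. A favourable arm 1 v arm 2 difference could be cited as evidence for clinical oversight when the app features or the care network contributed to it. A null difference could be misread as showing that triage does not help. Engagement with the platform, which the Strengths section puts first, is especially exposed. Arm 3 has no technology, so arm 1 v arm 2 is the only randomised contrast available for it. Arm 1 also has tailored measurement plans, highlighted exacerbations and caregivers who can see the data, each of which could plausibly raise use.

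**Working it through.** The article states no figure on this point, so the check is whether a triage effect can be estimated from the arms.

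**Inputs.** Components by arm, from the arm listing under p-RCT Design, Study Aim and Objectives, and the ProACT CareApp section (1 = provided or offered):

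| | Intercept | Base technology | Personalisation | Care network | Triage |
|---|---|---|---|---|---|
| Arm 1 | 1 | 1 | 1 | 1 | 1 |
| Arm 2 | 1 | 1 | 0 | 0 | 0 |
| Arm 3 | 1 | 0 | 0 | 0 | 0 |

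Base technology means the tablet, sensors, helpdesk and basic app.

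**Step 1: pairwise contrasts.** Subtracting rows, under additive component effects:

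- arm 1 − arm 2 = personalisation + care network + triage
- arm 1 − arm 3 = base technology + personalisation + care network + triage
- arm 2 − arm 3 = base technology

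**Step 2: any combination of arms.** Take a × arm 1 + b × arm 2 + c × arm 3. Personalisation, care network and triage appear only in arm 1, so each has the same coefficient, a. Isolating triage needs a = 1 for triage and a = 0 for the other two, which is impossible.

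**Step 3: the same result by rank.** The matrix has rank 3 for 5 parameters. Adding the triage-only row (0, 0, 0, 0, 1) raises the rank to 4, so triage is not estimable. For illustration only, a fourth arm equal to arm 1 without triage would make it estimable. Interactions between components would add unknowns and could not help.

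**Step 4: the planned model.** The Data Analysis Plan specifies a linear mixed model with time, arm-by-time interaction and baseline covariates. It compares arms and so inherits the limits of Step 2. No later analysis plan can create the missing contrast.

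**Step 5: variation within arm 1.** Two sources exist.

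- *Care network.* The p-RCT Methodology overview makes participation optional, so some arm 1 participants may have none. That is by choice. Comparing them with arm 2 gives up randomisation and still leaves the app differences mixed with triage.
- *Triage contact.* Under Data Flow Through the ProACT Platform and Trial Procedures, new readings are checked against thresholds, a breach raises an alert, and nurses contact participants about alerts. Contact therefore follows health status. It also depends on how often participants measure, so relating contact to engagement risks reverse causation.

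**The case against.** The strongest reply is that the trial never sets out to estimate triage alone. The stated aim and objectives compare packages, no planned primary analysis claims a triage-only effect, and the Strengths section itself elsewhere lists arm 1 as personalised app, care network and triage together. A pragmatic comparison of packages is legitimate. All of this stands. A reader might infer that the primary comparison is invalid; the documents do not support that.

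Second, this is a hybrid trial with a process evaluation. Triage use is logged, triage nurses are interviewed, and relations between delivery and effectiveness are to be explored. These data can describe the role of triage and generate hypotheses. They are not randomised, and for the reasons in Step 5 they cannot carry a conclusion about its effect.

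Third, the Strengths paragraph is hedged and concerns engagement, awareness and confidence, not the primary outcomes. That limits the seriousness of the point. It does not alter what the sentences attribute to triage.

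Fourth, the components overlap, because triage staff adjust thresholds and help to personalise data collection plans. Even if that part of personalisation is counted as triage, the app's highlighting and contextualised education and the care network remain bundled with it.

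Two further readings go too far. One is that every arm 1 participant receives the whole package; the care network is optional, so the package is offered. The other is that triage could account for any share of an arm 1 v arm 2 difference from none to all. Components may interact or act in opposite directions, so the documents support no such bounds.

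**Conclusion.** The point holds as a matter of interpretation, confined to two places in the Discussion. Arm 1 v arm 2 identifies the effect of being offered the added package: three components, one randomised contrast. The triage effect is not identified by any combination of the three arms. No numerical size can be put on the share due to triage.

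This rests on the arm definitions as published and on there being one three-arm randomisation; the article describes no factorial or second allocation. It does not depend on the sample size or on the choice of outcome model. The formal objectives and the primary comparisons stand.

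**What to change.** 1. Under Principal Findings and Strengths, replace the triage-specific effect claims with *the added support package (personalisation, care network and triage)*.
2. State what each contrast identifies: arm 2 v arm 3, the basic app plus devices; arm 1 v arm 2, the added package; arm 1 v arm 3, the full package.
3. Label any analysis of triage contacts or care network participation as observational and exploratory.
4. Add to Limitations that triage is bundled with the other arm 1 components and cannot be separated from them by randomisation.

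The cost is wording only, with no change to arms, sample size, data collection or primary model. What is lost is the triage-specific conclusion. The results are due for submission in 2026, so the same wording should carry into the results paper.
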